## Abstract

**Background:**

The expansion of digital devices and widespread access to the Internet has opened up opportunities to provide patients with more personal information. It can be hypothesized that eHealth in addition to standard care could enhance clinical outcomes such as increased weight loss, co-morbidity reduction, and commitment to the program. The beneficial value of incorporating eHealth applications as standard postoperative care is yet to be established. In this trial, the value of different levels of eHealth are assessed.

**Methods/design:**

Two hundred adult patients with a body mass index (BMI) ≥ 40 kg/m^2^, or ≥ 35 kg/m^2^ with obesity-related co-morbidity, undergoing sleeve gastrectomy or gastric bypass will be enrolled in this randomized controlled trial. Patients will be randomly assigned to one of the groups: receiving standard care (control group, *n* = 100); have access to an online eHealth platform in addition to the previous group (online group, *n* = 50); or receive wireless monitoring devices in addition to previous groups (device group, *n* = 50). The total follow-up period is two years postoperatively. Primary outcome is weight loss in terms of BMI. Secondary outcomes include: quality of life; return-to-work time; co-morbidity reduction; additional contacts; and ease of use of devices.

**Discussion:**

In this trial, the value of different levels of eHealth will be assessed. This addresses an important aspect of a changing healthcare environment.

**Trial registration:**

Trialregister.nl, NTR6827. Retrospectively registered on 19 November 2017. http://www.trialregister.nl/trialreg/admin/rctview.asp?TC=6827.

**Electronic supplementary material:**

The online version of this article (10.1186/s13063-018-3020-x) contains supplementary material, which is available to authorized users.

## Background

Bariatric surgery is the only treatment with long-standing effect on morbid obesity. The key elements to success are the patient selection, an experienced bariatric team, and a completed follow-up program. Follow-up programs can consist of, for example, providing social support in support groups, teaching psychological skills, such as coping with the body change, or teaching self-regulation of body weight [1–5]. Furthermore, follow-up is important for dietary and sports counseling [2, 5]. The experience of the team members and coaching skills are essential in indicating the suitable procedure if necessary and guiding patients through the process. Various studies have found a significant positive effect of a completed follow-up program after bariatric surgery on maintaining weight loss [6, 7]. There is a burden for this on-site provided care as organizational and financial resources are not unlimited, especially as the follow-up period is an obligatory five years or, if possible, lifelong. Even if this aftercare is provided, not all patients complete the entire program. Various reasons are possible for an increasing no-show rate; loss of enthusiasm for on-site visits could be one of them.

Analogous to other chronic diseases, the addition of telehealth could be useful for the treatment of obesity. Telehealth is the delivery of health-related services and information via telecommunication technologies. It encompasses preventative, promotive, and curative aspects. Examples are exchanging health services or education via videoconference, transmission of medical data for disease management (remote monitoring) and advice on prevention of diseases, and promotion of good health by patient monitoring and follow-up. Participation with eHealth has been investigated and considered useful in the treatment of obesity [4, 8–13]. In a systematic review, self-measured blood pressure monitoring was associated with better control of hypertension in the first year [14]. Its value in a bariatric trajectory has not been investigated. It can be hypothesized that self-control by eHealth could enhance clinical outcome through more weight loss and co-morbidity reduction. Long-term realistic goal setting, consistent use of routines, and self-monitoring have been proven effective for weight loss maintenance [15]. Patients with higher self-control are more confident regarding their abilities, which leads to higher commitment and adherence to the program. This eventually leads to more weight loss  [4]. For this purpose, an online monitoring program was designed for our obesity department to provide preoperative information as well as aid in the post-bariatric phase by self-control wireless devices for registration of biometric outcomes, teleconference opportunities, and access to additional information.

The objective of this trial is to determine whether patients benefit from different degrees of eHealth and self-monitoring. This research will contribute to the still small body of evidence around the value of eHealth.

## Methods/design

### Study aim

The aims of the BePatient trial are to assess the value of eHealth by comparing different levels of telehealth provided to bariatric patients. It is hypothesized that the more eHealth is provided, the higher postoperative weight loss will be, the less likely additional contacts/visits will be consumed, the higher the patients’ satisfaction will be, and the more benefits in co-morbidity will be found. The addition of eHealth provides the patients more self-control, which could result in better commitment to the follow-up program. The primary study hypothesis is that the benefit of adding eHealth to a bariatric care program would lead to a larger reduction in body mass index (BMI) two years after the procedure compared to standard care.

Two main research questions are addressed:Does an eHealth platform increase weight loss after bariatric surgery?Does providing patients with electronical wireless monitoring devices lead to more weight loss?

### Study setting

This open-label randomized controlled trial is conducted at the Catharina Hospital Eindhoven, a large teaching hospital in the Netherlands. Around 1000 bariatric procedures are performed annually by dedicated bariatric surgeons.

### Study registration

The study was reviewed and approved by the institutional medical ethical board. The protocol (protocol identification number: NL56992.100.16, version 3, 11 July 2016) conforms to the principles of Good Clinical Practice and the Declaration of Helsinki. Table 1 shows a structured summary conforming with a standard WHO trial registration dataset. Retrospective registration was achieved in the Dutch trial registration on 19 November 2017 (Identifier number NTR6827.) The trial is ongoing and currently recruiting. The first patient was included on 21 February 2017. In case of amendments to the protocol, the institutional medical ethical board will be notified for approval. This protocol was conducted conforming the SPIRIT 2013 Checklist (Additional file 1).

**Table 1 Tab1:** WHO trial registration dataset – structured summary

Data category	Information
Primary registry and trial identifying number	Nederlands trial register - NTR6827
Date of registration in primary registry	19 November 2017
Secondary identifying numbers	Clinicaltrials.gov: NCT03394638 Protocol number: NL56992.100.16
Source(s) of monetary or material support	N/A
Sponsor	N/A
Contact for public/scientific queries	Obesity Center, Catharina Hospital Eindhoven, The Netherlands
Public title	BePatient trial
Scientific title	Assessing the value of eHealth for bariatric surgery (BePatient trial): study protocol for a randomized controlled trial
Country of recruitment	The Netherlands
Health condition(s) or problem(s) studied	Morbid obesity
Intervention(s)	Standard care vs eHealth platform vs eHealth platform + self-monitoring devices
Key inclusion and exclusion criteria	Age > 18 years; eligible for bariatric surgery; BMI > 40 kg/m^2^ or > 35 kg/m^2^ with related co-morbidity; ongoing access to the Internet; ability to use smartphone or tablet; ability to understand Dutch language; signed informed consent
Study type	Open randomized controlled trial
Date of first enrollment	21 February 2017
Sample size	200
Recruitment status	Recruiting
Primary outcome(s)	BMI
Key secondary outcomes	Sociodemographics, weight, co-morbidity status, quality of life, return to work, satisfaction and commitment, inventory of use of additional support, devices and data-traffic
Ethics review	Reviewed and approved by Institutional Review Board on 15 August 2016
Summary results	Planned to be released in 2020
IPD sharing statement	Undecided

### Study population

Obese adults with a BMI > 40 kg/m^2^, or > 35 kg/m^2^ with at least one obesity-related co-morbidity, such as hypertension or diabetes, unsuccessful previous attempts to lose weight, and willingness to attend a follow-up program could be indicated for a bariatric procedure. Patients referred to the Catharina Obesity Center are asked for access to the Internet and willingness to complete the mandatory screening questionnaire online. From the beginning of 2015, this was the standard procedure of the center. In case of inability or unwillingness to use the online version, the patient receives a postal alternative. After returning the questionnaires, patients are invited to the outpatient department. There they receive a presentation and interview by an obesity nurse, dietician, psychologist, and physiotherapist and receive extensive blood tests. These results are discussed in an obesity team with bariatric surgeons. After approval for the operation by this multidisciplinary team, patients visit the bariatric surgeon. If the result of this consult is a planned operation, the patient could be considered eligible for participation to this study. The sleeve gastrectomy and bypass are by far the most performed initial procedures at this center. Therefore, only patients with approval for a primary gastric sleeve or bypass are finally considered to be eligible. Figure 1 shows a flowchart illustrating the recruitment and allocation process in this trial. Figure 2 shows the SPIRIT schedule of enrollment, interventions, and assessments used in this trial.

**Fig. 1 Fig1:**
[figure not shown]
*Flowchart* illustrating the recruitment and allocation process in this trial

**Fig. 2 Fig2:**
[figure not shown]
Standard Protocol Items: Recommendations for interventional Trials (SPIRIT) figure

### Inclusion criteria

The inclusion criteria to participate in this study are:Completed the mandatory questionnaire online;Having ongoing access to the Internet;Ability to use a model of mobile device (smartphone or tablet);A BMI > 40 kg/m^2^ or > 35 kg/m^2^ with related co-morbidity (hypertension, diabetes type 2, hyperlipidemia, obstructive sleep apnea syndrome, or arthralgia of lower limbs;A primary gastric sleeve or bypass planned;Age ≥ 18 years;Ability to read and write the Dutch language; andSigned informed consent.

Those who did not met the abovementioned inclusion criteria were excluded.

### Inclusion procedure

Patients are informed about the study at two separate times. During the screening phase, patients receive a leaflet with information about the study and are informed during a group meeting with other patients. Later, if a procedure is planned and the operation date is known, patients are again informed by a trained member of the research team in an individual consultation. Afterwards patients are given the time to consider participating. If they decide to participate, written informed consent is obtained (see Additional file 2). Patients are informed that they can stop at any time without any effect on their usual care and without being required to provide a reason for stopping. After completion of the study, patients will receive standard care. There is no financial benefit or other compensation for participating in this trial.

### Randomization and treatment allocation

Participants who fulfill all selection criteria and signed the informed consent form are randomized in a 2:1:1 ratio. Simple randomization is used, meaning every individual has an equal chance to be enrolled in one of the three groups. Allocation is into one of three groups: (1) control group (*n* = 100); (2) platform group (*n* = 50); and (3) device group (*n* = 50). This randomization is computer-generated in a Care Coordination Module functionality in the BePatient platform. Allocation concealment will be ensured, as the allocation of patients is generated after the patient signs the informed consent form and thereby included in the study.

### Safety assessment

Severe adverse events (SAE) within this study are assumed to be difficult to determine ahead of time. Personal injury through use of the devices is the only predetermined category; other AEs will be identified upon the decision of the treating team. In case of an AE, this will be reported to the ethics committee and included in the results. Due to the expected absence of any SAE, there is no annual safety report or monitoring board.

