The success of bariatric surgery depends on motivation. An attempt to increase this motivation is to add eHealth applications and self-monitoring devices. However, study patients can experience this as mandatory which can imply a counterproductive effect on their incentive. In this respect, patients are informed very well about the voluntariness to use the devices and patient website. However, patients may lose interest after some time during the total lifespan of the study of two years. Also, another possible drawback of the use of devices can be that they generate an opposing effect on patients. The increased awareness of their weight can lead to some sort of compulsive need to keep losing more weight. We advise patients to not weigh themselves on a daily basis because natural changes in their weight can result in a false understanding of gaining weight. This drawback is, however, an important aspect of this study. If the devices turn out to give patients more negative than positive effects, this will result in valuable information.

It can be stated that during the first years after the operation weight loss is majorly depending on the procedure itself and other factors, such as patients’ adherence or physical activity, only start to play an increasingly substantial role in weight sustain and regain after the first year. Therefore, it might be interesting to extend to study span to the full follow-up period of five years after the initial two-year study span.

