## Abbreviations

BMI: Body mass index
SAE: Severe adverse event

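### The reason given for waiving safety reporting, that no SAE is expected, holds only if SAE means intervention-related, which the text does not say; adverse events other than device injury have no common criterion across arms

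*Protocol article*

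**What the plan says.** The Safety assessment section of the protocol article makes four statements that matter here.

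- On predictability: "Severe adverse events (SAE) within this study are assumed to be difficult to determine ahead of time".
- On what is captured: "Personal injury through use of the devices is the only predetermined category", and "other AEs will be identified upon the decision of the treating team".
- On what happens to an event once identified: "In case of an AE, this will be reported to the ethics committee and included in the results".
- On oversight: "Due to the expected absence of any SAE, there is no annual safety report or monitoring board".

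The Data collection section adds an annual status report to the ethics committee, which is not described as a safety report. The Abbreviations list expands the term only as "SAE: Severe adverse event"; no definition is given.

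The Discussion names a possible harm of the monitoring devices: "The increased awareness of their weight can lead to some sort of compulsive need to keep losing more weight". It calls this an important part of the study and says that a net negative effect of the devices would be worth knowing. The Safety assessment section does not mention it.

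**The concern.** An event type that is hard to predict cannot, on the same grounds, be expected not to happen. The premise also fits badly with the design. Every participant enters with a sleeve gastrectomy or bypass planned, and the operation and the two years after it appear to fall inside the trial. Deaths, readmissions and reoperations are ordinary possibilities over that period whatever their cause, and the text does not set surgical events aside.

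The premise has consequences, because it is the stated reason for having no annual safety report. The section also gives no common criterion for finding events. Only device injury is fixed in advance, and the trial supplies devices to one arm of 50. Everything else depends on judgement by clinicians who can know the allocation. At stake is whether the adverse events in the final report can be compared between arms.

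The harm named in the Discussion has a related difficulty. The primary hypothesis treats a larger fall in BMI as benefit, so weight loss driven by compulsion would count in favour of the devices unless some other comparison is designated to show the harm.

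**Working it through.** **Inputs from the protocol article**

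- Total sample: 200, as 100/50/50 (Abstract; Randomization and treatment allocation; Sample size calculation). The inflation for missing data reproduces: 96/0.96 = 100 and 48/0.96 = 50, so 100 + 50 + 50 = 200.
- Surgery: a primary sleeve or bypass is still planned at entry (Inclusion criteria).
- Consent: sought once the operation date is known (Inclusion procedure).
- Allocation: generated after the consent form is signed (Randomization and treatment allocation).
- Follow-up: two years after surgery (Abstract).
- SAE rate: none given. The only safety figure is an expectation of zero, without a source.

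**Step 1: does surgery fall inside the trial?** No single sentence says so. It follows from planned surgery at entry, consent before the operation, and allocation on consent. A few participants might not be operated on.

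**Step 2: how plausible is zero on an all-cause reading?** Let q be the two-year risk per patient. The expected number affected is 200 × q, and P(at least one) = 1 − (1 − q)^200. The values of q are assumptions.

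| Assumed q | Expected patients | P(none) | P(at least one) |
|---|---|---|---|
| 0.1% | 0.2 | 82% | 18% |
| 0.5% | 1 | 37% | 63% |
| 1% | 2 | 13% | 87% |
| 2% | 4 | 1.8% | 98% |
| 5% | 10 | 0.004% | >99.9% |

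**Step 3: what risk would the premise need?** Zero events is more likely than not only if q is below 1 − 0.5^(1/200) = 0.35%. It has 95% probability only if q is below 1 − 0.95^(1/200) = 0.026%.

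**Step 4: what can by-arm reporting show?** At q = 1% to 5%, the expected counts are 1 to 5 in the control group (100 × q) and 0.5 to 2.5 in each group of 50 (50 × q). Zero events in 50 device patients leaves a one-sided 95% upper limit of 1 − 0.05^(1/50) = 5.8%. By-arm reporting is therefore descriptive. That limit comes from the arm size and would remain after any change in how events are recorded.

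**Step 5: is the named harm covered by an outcome?** RAND-36, including its mental health domain, is collected at baseline, one year and two years (Quality of life). The Data analysis section plans group comparisons of the outcome measures. A relevant between-arm comparison therefore exists, but the article does not tie it to the harm that the Discussion raises.

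**The case against.** The best reply is that SAE here means an event caused by eHealth. The one predefined category concerns the devices, and surgery is planned in every arm as part of usual treatment. On that reading, expecting none is reasonable, and the all-cause risks above do not bear on it. At a risk of 0.1%, even an all-cause count would more likely than not be zero. This reading is plausible, but the text does not state it: the waiver refers to the absence of any SAE and exempts no surgical events.

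A second reply is that the article condenses a fuller protocol that is not shown. That disposes of any complaint about absent forms or definitions. It does not reach the stated premise or the stated rule for identifying events.

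Several stronger readings are tempting and are not supported:

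- *Only device injury is reported.* Any identified adverse event goes to the ethics committee and into the results.
- *The trial defines SAEs by severity.* The article only expands an abbreviation.
- *Events will be recorded differently by arm.* This is a risk, not a fact. All arms receive the same standard care programme. The medical team has access to platform data, but the article does not say that it reviews device readings.
- *Nothing measures the named harm.* RAND-36 and BMI are already compared between groups. What is lacking is a designated harm comparison.
- *The trial needs a monitoring board.* Its absence is not an error in a low-risk trial; the fault lies in the reason given.
- *The trial fails a safety aim.* The Study aim section states none.

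**Conclusion.** The point holds in a limited form. The stated ground for waiving an annual safety report conflicts with the opening sentence of its own section. On an all-cause reading it also conflicts with a design that contains bariatric surgery and two years of follow-up. At assumed all-cause risks of 1% to 5%, 2 to 10 of 200 patients would be affected, with an 87% to over 99.9% chance of at least one. The premise survives only if SAE means intervention-related, and the article does not say so.

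Separately, leaving all events other than device injury to the judgement of an unblinded team is a stated rule under which capture may be incomplete and may differ by arm. The Safety assessment and Discussion sections also need to be reconciled on the harm that the latter names.

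The conclusion rests on surgery following allocation, which is inferred from several sections, and on event rates that are assumptions. A reader might infer that the trial's main result is compromised. It is not: the primary BMI analysis does not depend on any of this.

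**What to change.** 1. In the Safety assessment section, replace the premise with a statement of whether SAE means all-cause or intervention-related, and clarify the term, which is now expanded only as severe. If surgical events are to be exempt from expedited reporting, say so.
2. Use one predefined criterion in all three arms: extract deaths, readmissions and reoperations from the existing hospital files at one and two years, irrespective of attribution.
3. Report these by randomized arm as counts and proportions with confidence intervals, without a claim of equivalence, since the arms are too small for one.
4. Name the planned between-arm comparison of the RAND-36 mental health domain as the harm comparison for the device group, and cross-refer to it from the Discussion. It is not specific to compulsive weight loss, but it is already collected and does not count further weight loss as a gain. A new excessive-weight-loss endpoint is not needed; it would require a cut-off that the documents do not supply.

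The cost is a short amendment and some data-entry time for chart extraction. It needs no new visits, no monitoring board and no change to the primary analysis.

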### Interventions

#### Standard care

All patients will receive standard care which consists of a five-year follow-up scheme after the bariatric procedure. The first year consists of around 10 individual and three group consultations. These follow-up visits are usually at around 1, 3, 6, 8, 9, 10, 12, 16, 20, and 24 months postoperatively and include consultations with their surgeon, dieticians, physiotherapists, and obesity nurses. After the first year, visits become less frequent. If deemed necessary, additional contact can be made. During the total follow-up time, blood markers are frequently assessed.

